# Sanjin tablets for acute uncomplicated lower urinary tract infection (syndrome of dampness-heat in the lower jiao): protocol for randomized, double-blind, double-dummy, parallel control of positive drug, multicenter clinical trial

**DOI:** 10.1186/s13063-019-3539-5

**Published:** 2019-07-19

**Keywords:** Acute uncomplicated UTI, Syndrome of dampness-heat in the lower jiao, Randomized controlled trial, Clinical trials, Sanjin tablets

## Abstract

**Background:**

Acute uncomplicated lower urinary tract infection (UTI) is one of the most common bacterial infections. Patients usually present with dysuria, urinary urgency, urinary frequency, and suprapubic pain or tenderness. Approximately 150 million people are diagnosed with UTI each year worldwide. The high recurrence rate of lower UTI is a common problem of clinical treatment. The misuse of antibiotics has led to the emergence of a number of resistant bacterial strains. Thus, traditional Chinese medicine is considered as an alternative option for treating acute uncomplicated lower UTI. Thus, this study aims to evaluate the efficacy and safety of Sanjin tablets (SJT) for the treatment of acute uncomplicated lower UTI, explore whether SJT can reduce or substitute the use of antibiotics, and reduce the recurrence rate in the treatment of acute uncomplicated lower UTI.

**Methods/design:**

In this study, a randomized, double-blind, double-dummy, parallel control of positive drug, multicenter clinical study will be established. A total of 252 patients with acute uncomplicated lower UTI (syndrome of dampness-heat in the lower jiao) will be randomly allocated in the ratio of 1:1:1 to three groups: experimental group; control group 1; and control group 2. The experimental group receives Sanjin tablets plus levofloxacin tablets (LT) placebo; the control group 1 receives LT plus SJT placebo; and the control group 2 receives SJT plus LT on the first five days, SJT plus LT placebo on the last two days. Each group will be treated for seven days and followed-up 1–2 times. The primary outcome measures of effective rate and recurrence rate are symptoms. Secondary outcome measures of effective rate and recurrence rate are the urine leukocytes, bacteriology examination, and safety assessment. Outcomes will be assessed at baseline and after treatment.

**Discussion:**

This study protocol will provide the research data of efficacy and safety of SJT for the treatment of acute uncomplicated lower UTI. The first aim is to determine whether Sanjin tablets can reduce the use of antibiotics; the second aim is to determine whether Sanjin tablets can substitute the use of antibiotics. The recurrence rate will be assessed after cured to determine whether SJT can reduce the recurrence rate. The results of this study will improve the rational use of drugs, especially the rational application of antibiotics. It will also enable safety evaluation from laboratory indices and adverse events, which will provide reliable evidence for clinical treatment.

**Trial registration:**

ClinicalTrials.gov, NCT03658291. Registered on 4 September 2018.

**Electronic supplementary material:**

The online version of this article (10.1186/s13063-019-3539-5) contains supplementary material, which is available to authorized users.

## Background

Acute uncomplicated lower urinary tract infection (UTI) is one of the most common bacterial infections. Patients usually present with dysuria, urinary urgency, urinary frequency, and suprapubic pain/tenderness [1]. In the United States, there are > 7 million outpatients with UTIs and about 1 million inpatients each year [2]. Approximately 150 million people are diagnosed with UTI each year worldwide [3]. UTI, which can cause shock and death, ranks third among all diseases that die from infection [4]. Gram-negative bacteria, especially Enterobacteriaceae, is the common cause of both community-acquired and hospital-acquired UTIs [3, 5]. Many Chinese medicines that have a heat-clearing and detoxicating function have been proven to have the bacteriostasis on pathogenic microorganisms, which can inhibit or destroy the formation of toxic substances [6, 7]. In the antibacterial test against mice, it was found that Sanjin tablets (SJT) have strong bacteriostasis activity [8].

SJT have the effects of clearing heat, detoxicating, eliminating dampness, and treating stranguria [9]. It is used to treat urinal urgency, frequency, and burning caused by syndromes of dampness-heat in the lower jiao, which coincides with the symptoms of acute uncomplicated lower UTI. SJT are composed of five kinds of Chinese herbal medicines: Jinyinggen (Root of Cherokee Rose), Baqia (Chinaroot Greenbrier Rhizome), Yangkaikou (Fruit of Fiverleaf Akebia), Jinshateng (Lygodii Herba) and Jixuecao (Asiatic Pennywort Herb), all of which are recorded in the Chinese Pharmacopoeia (V.2015). Jinyinggen (Root of Cherokee Rose) is acerb and neutral in nature; it can control nocturnal emission and astringent intestine. Baqia (Chinaroot Greenbrier Rhizome) is cosin and neutral in nature; it can remove rheumatism, promote blood circulation, detoxicate, relieve convulsion, and calm endogenous wind. Jinshateng (Lygodii Herba) is slightly sweet and cold-natured; it can clear heat, detoxicate, and remove dampness. The above three herbs are monarch drugs in a prescription, which have a mutual promotion effect on the function of clearing heat, removing dampness, and inducing diuresis for treating stranguria. The above three medicines, supplemented with Yangkaikou (Fruit of Fiverleaf Akebia) and Jixuecao (Asiatic Pennywort Herb), can enhance the effects of removing dampness and treating stranguria [10, 11].

SJT are a completely natural preparation with significant efficacy in treating UTI [12]. Previous clinical studies have indicated that SJT can reduce the symptoms of chronic UTI and number of acute attacks and can reduce the secretory level of urinary sIL-2R, IL-6, IL-8 in patients with chronic nephropyelitis [8]. Observation by electron microscope found that SJT can make *Escherichia coli* flagella drop without any danger. A meta-analysis has demonstrated that the current evidence is insufficient to support the efficacy and safety of SJT for acute uncomplicated lower UTI due to lack of high-quality randomized controlled trials (RCT) [13]. The high recurrence rate of lower UTI is a common problem of clinical treatment [14]. The misuse of antibiotics has led to the emergence of a number of resistant bacterial strains [15]. Unfortunately, the efforts to produce new antibiotics have not been sufficient to cope with the emergence of these new antibiotic-resistant (AR) strains [16]. Therefore, the objective of our study is to evaluate effectiveness, safety, and recurrence rate of SJT and explore whether SJT can reduce or substitute the use of antibiotics for acute uncomplicated lower UTI by a rigorous RCT.

## Method/design

### Objective and design

This is a randomized, double-blind, double-dummy, parallel control of positive drug, multicentre clinical study. The study will be conducted at: the XiYuan Hospital, China Academy of Chinese Medical Sciences; the Longhua Hospital Shanghai University of Traditional Chinese Medicine; the Guangdong Provincial Hospital of Traditional Chinese Medicine; the Hubei Hospital of Traditional Chinese Medicine; the Affiliated hospital of Chengdu University of Traditional Chinese Medicine; and the Yunnan Provincial Hospital of Traditional Chinese Medicine. Ethical clearance for the trial was obtained from ethics committee of the six hospitals. Patients with acute uncomplicated lower UTI will undergo a standardized baseline evaluation before treatment, comprising detailed history taking, physical examination, and laboratory testing. All included patients are randomly divided into three groups: experimental group; control group 1; and control group 2. The experimental group receives SJT plus levofloxacin tablets (LT) placebo; control group 1 receives LT plus SJT placebo; and control group 2 receives SJT plus LT on the first five days, SJT plus LT placebo on the last two days. After seven days of treatment, the efficacy and safety of three groups will be evaluated. The first aim is to determine whether SJT can reduce the use of antibiotics (control group 2 versus control group 1, non-inferiority test); the second aim is to determine whether SJT can substitute the use of antibiotics (experimental group versus control group 1, non-inferiority test). The recurrence rate will be assessed at the 28-day follow-up after being cured to determine whether SJT can reduce the recurrence rate. The trial is conducted in accordance with the World Medical Association Declaration of Helsinki and Good Clinical Practice of Pharmaceutical Products [17, 18]. After a full explanation by the clinicians, written informed consent will be obtained from the participants before intervention [19, 20]. Strict data management and quality control will be conducted in this trial [21, 22]. This trial was registered in the Clinical Trials USA registry (registration No. NCT03658291) on 4 September 2018 and will be carried out from January 2019 to December 2019. The study design is shown in Fig. 1. The protocol follows the recommendations of the SPIRIT initiative (see Additional file 1) [23] and the trial results will be reported according to the latest version of the CONSORT statement [24].

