### Interventions

All researchers are clinical doctors and receive standardized training for the diagnostic interview before the start of the trial. LT are licensed for UTI with proven curative effect and safety [32]. Therefore, levofloxacin had been selected as the active control medicine. Participants in the experimental group will receive SJT plus LT placebo orally four times a day for seven days. Participants in control group 1 will take LT plus SJT placebo four times a day for seven days. Participants in control group 2 will take SJT and LT four times a day for the first five days and SJT plus LT placebo four times a day for the last two days. Patient visits are required after seven days of treatment. This is a placebo-controlled study; all participants receive the same number of pills with varying proportions of active drug and placebo to ensure that patients and clinicians are not aware of the allocated treatment aim. The SJT placebo is composed of 55% microcrystalline cellulose, 41% starch, 2% caramel, 1.5% silicon dioxide, and 0.5% talcum powder. The LT placebo is made of 56% microcrystalline cellulose, 42% starch, 1.5% silicon dioxide, and 0.5% talcum powder. The SJT and LT placebos are similar to the SJT and LT in size, color, shape, taste, smell, and packaging. SJT and its placebo and the LT placebo are produced by Guilin Sanjin Pharmaceutical Co., Ltd. and can be preserved for two years. LT is provided by First Sankyo Pharmaceutical (Beijing) Co., Ltd. at a dosage of 100 mg and can be preserved for two years. The recommended dosage of LT is 2–3 times a day, one pill at a time; hence, in order to meet the requirements of the blinding, the administration method of this medicine has been designed as described in Table 1.

**Table 1 Tab1:** Administration methods in the experimental and control groups

Time	Experimental group	Control group 1	Control group 2	
			First 5 days	Last 2 days
08:00	3 pills of SJT, 1 pill of LT placebo	3 pills of SJT placebo, 1 pill of LT	3 pills of SJT, 1 pill of LT	3 pills of SJT, 1 pill of LT placebo
12:00	3 pills of SJT	3 pills of SJT placebo	3 pills of SJT	3 pills of SJT
17:00	3 pills of SJT, 1 pill of LT placebo	3 pills of SJT placebo, 1 pill of LT	3 pills of SJT, 1 pill of LT	3 pills of SJT, 1 pill of LT placebo
22:00	3 pills of SJT	3 pills of SJT placebo	3 pills of SJT	3 pills of SJT

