## Strengths and limitations of this study

This is a well-designed study to assess the efficacy, safety, and recurrence rate of SJT for acute uncomplicated lower UTI in adults.The results from this randomized, double-blind, double-dummy, parallel control of positive drug, multicenter clinical trial will provide new evidence of the efficacy and recurrence rate of SJT for acute uncomplicated lower UTT.This study will provide evidence of SJT for reducing or substituting the use of antibiotics for acute uncomplicated lower UTI, which can guide rational application of antibiotics.This trial will be implemented in six hospitals in Chinese patients; this can strengthen its generalizability.One limitation is the results of participant symptoms evaluate scales might have subjective factors.Another limitation is the participant symptoms evaluate scales, which might exaggerate the severity of the symptoms of acute uncomplicated lower UTI.

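### Aim 1: non-inferiority of control group 2 to control group 1 cannot by itself be credited to SJT, because the two arms differ in two factors and no arm gives five days of levofloxacin with SJT placebo

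*Protocol article*

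**What the plan says.** The protocol article has three arms: "All included patients are randomly divided into three groups: experimental group; control group 1; and control group 2". Their content is the same in the Abstract, in Objective and design, and in Interventions with Table 1:

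- Experimental group: "Participants in the experimental group will receive SJT plus LT placebo orally four times a day for seven days".
- Control group 1: "Participants in control group 1 will take LT plus SJT placebo four times a day for seven days".
- Control group 2: "control group 2 receives SJT plus LT on the first five days, SJT plus LT placebo on the last two days".

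Objective and design ties each aim to one comparison. For aim 1: "The first aim is to determine whether SJT can reduce the use of antibiotics (control group 2 versus control group 1, non-inferiority test". For aim 2: "the second aim is to determine whether SJT can substitute the use of antibiotics (experimental group versus control group 1, non-inferiority test". The Discussion repeats both pairings. The Discussion part of the Abstract gives the same two aims without naming the arms, and the Background sections of the Abstract and of the main text carry the same objective in softer words. Strengths and limitations of this study goes furthest: "This study will provide evidence of SJT for reducing or substituting the use of antibiotics for acute uncomplicated lower UTI".

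On what is already known, the Background reports a meta-analysis finding that "the current evidence is insufficient to support the efficacy and safety of SJT for acute uncomplicated lower UTI".

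**The concern.** In every statement of aim 1, SJT is what is said to reduce antibiotic use. The comparison offered as proof is between two regimens that differ both in SJT and in the length of active levofloxacin. If control group 2 proves non-inferior, there are at least two explanations: SJT made up for the two missing days of levofloxacin, or those two days made little difference and SJT did nothing. The design has no arm that tells these apart.

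Aim 1 is the trial's first-named aim, and its result is offered as a guide to rational antibiotic use. Even a clean non-inferiority result would not support the conclusion as worded.

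**Working it through.** **Step 1. Content of each arm (Objective and design; Interventions; Table 1).**

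| Arm | Active SJT | Active levofloxacin |
|---|---|---|
| Experimental group | 7 days | 0 days |
| Control group 1 | 0 days (placebo) | 7 days |
| Control group 2 | 7 days | 5 days, then placebo for 2 days |
| *Not in the trial* | *0 days (placebo)* | *5 days* |

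**Step 2. What the aim 1 contrast measures.** Let R(SJT, days) be the effective rate with or without SJT and with a given number of levofloxacin days. Then

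R(yes, 5) − R(no, 7) = [R(yes, 5) − R(no, 5)] + [R(no, 5) − R(no, 7)].

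The first bracket is what SJT adds to five days of levofloxacin. The second is the effect of the shorter course. R(no, 5) is not observed in any arm, so the data give the sum but neither part. If the second bracket is near zero, the regimens are truly non-inferior even when the first bracket is exactly zero.

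**Step 3. Do the documents supply the missing link?** Crediting SJT needs the premise that five days of levofloxacin alone is meaningfully worse than seven. The article neither states nor assumes this, and gives no efficacy figure by levofloxacin duration. Nor can an SJT effect be presumed, since the Background calls the evidence insufficient.

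**Step 4. Does aim 2 help?** Aim 2 estimates R(yes, 0) − R(no, 7). It does not contain R(no, 5) and says nothing about what SJT adds to five days of levofloxacin. There is also no arm without active treatment against which SJT alone could be judged.

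**Step 5. Illustration only.** The plan gives no figure for this point, so there is none to reproduce. Suppose SJT is inert and five- and seven-day levofloxacin share one rate p. The chance of declaring non-inferiority is then

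Φ(M/SE − z(1−α)), with SE = √(2p(1−p)/n).

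Inputs:

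- p = 0.7714. This is the SJT rate in Sample size, assumed here for levofloxacin because no levofloxacin rate is given.
- n = 84 per arm (252/3, all randomised), or 67 (84 × 0.8 = 67.2, after the 20% drop-out in Sample size).
- One-sided α = 0.025 (half the two-sided 0.05 in Data analysis), or 0.005 (half the two-sided 0.01 in Sample size). The z-values are 1.960 and 2.576.
- Margin M = 10, 15 or 20 points. These are assumptions, as the article states no margin.

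Standard errors: n = 84 gives √(2 × 0.7714 × 0.2286/84) = 0.0648; n = 67 gives 0.0726.

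| n per arm | one-sided α | M = 10 | M = 15 | M = 20 |
|---|---|---|---|---|
| 84 | 0.025 | 0.34 | 0.64 | 0.87 |
| 84 | 0.005 | 0.15 | 0.40 | 0.70 |
| 67 | 0.025 | 0.28 | 0.54 | 0.79 |
| 67 | 0.005 | 0.12 | 0.31 | 0.57 |

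The lowest cell is Φ(0.10/0.0726 − 2.576) = Φ(−1.20) = 0.12. The highest is Φ(0.20/0.0648 − 1.960) = Φ(1.13) = 0.87.

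**The case against.** The best defence is that aim 1 is a regimen question. Objective and design names the two arms in parentheses, so the contrast is open to view. Read pragmatically, it asks whether a regimen with SJT and fewer levofloxacin days holds up against the full course, and for that question the comparison is sound. Some passages are also cautious: the Background speaks of exploring, and the Discussion says the results may provide evidence. This stands as a defence of the comparison, and the fix keeps the comparison unchanged. It does not rescue the wording. No passage says that only the combined regimen is being judged, the sentence in Strengths and limitations is not hedged, and the two limitations listed there concern only the symptom scales.

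A second objection is that the probabilities are nothing more than non-inferiority power for two equal regimens and move widely with the inputs. That is right. They do not measure the attribution problem, and no single cell should be quoted as its size. Nor can the likelihood of the rival explanation be judged from the article.

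A third is that a separate analysis plan might deal with this. A plan can limit the interpretation, but it cannot recover a contrast that no arm provides. The arms, the comparison and the claim are all stated here.

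A reader might also infer more than the design implies, namely that the trial could never show any contribution from SJT. That goes too far. Superiority of control group 2 over control group 1 could suggest one, provided seven days of levofloxacin is at least as good as five. But superiority is not the stated test for aim 1.

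**Conclusion.** The point holds for non-inferiority alone. Control group 2 against control group 1 changes two factors together, the arm that would separate them does not exist, and aim 2 does not fill the gap. A non-inferiority result would support a statement about the combined regimen, not the statement that SJT reduced antibiotic use.

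This conclusion rests on the arm structure and needs no number. The 12% to 87% range shows only that an inert SJT could pass aim 1 with a chance that is far from negligible under many inputs. It depends on assumed margins, on a levofloxacin rate borrowed from SJT, and on equal efficacy of the two course lengths.

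The documents do not support the inference that SJT is inert, that five days of levofloxacin is in fact sufficient, or that the regimen comparison is invalid. They are silent on the first two, and the comparison is legitimate for the narrower claim.

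**What to change.** Restate aim 1, and the conclusion it can support, as a regimen comparison: SJT plus five-day levofloxacin is, or is not, non-inferior to seven-day levofloxacin. Make the change wherever the objective or claim appears: the Background and Discussion parts of the Abstract, the main Background, Objective and design, the Discussion, and Strengths and limitations of this study.

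In Strengths and limitations, add that the design cannot separate an effect of SJT from the shorter levofloxacin course being sufficient.

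No new arm and no change to treatment, endpoint, sample size or test is proposed. The cost is a few sentences and a narrower claim.

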
**Fig. 1 Fig1:**
[figure not shown]
Flow diagram. SJT Sanjin tablets, LT levofloxacin tablets

## Patient and public involvement

Patients were not involved in the research question, design, conduct, outcome measures, and data analysis of the study. Only medically trained clinicians carry out the patient recruitment and management in the study. The clinicians will describe the purpose, burden of the intervention, procedure, and potential risks of this trial to the participants themselves or their designated representative before the recruitment. We will disseminate the results of this study to participants through patient organizations and open lectures.

### Sample size

The effective rate will be taken as the main outcome measure of the clinical trial. According to a previous study, it showed that the effective rate of SJT was 77.14% in the treatment of simple bacterial lower urinary tract infection [25]. On the basis of a 0.9 power to detect a significant difference (α = 0.01, two-sided), 76 participants will be required for each group. 228 participants will be required for the three groups in a 1:1:1 ratio. Considering a 20% drop-out rate, we plan to include 252 patients in the whole trial.

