## Outcome measures

### Effective rate

The effective rate will be evaluated from three dimensions: symptoms; urine leukocytes; and bacteriological examination.

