#### Primary outcome measure

The symptoms of acute uncomplicated lower UTI will be assessed. The assessment tools for symptoms of acute uncomplicated lower UTI are three participant self-rating scales (see Additional file 2): criteria sheet for evaluating the severity of urinary system infection (CSESUSI; mild: total score ≤ 8, moderate: total score 9–15, severe: total score ≥ 16), if the severity of the disease decreases from severe to moderate, or from moderate to mild, the symptoms are improved; symptoms score sheet of TCM (SSST; cure: total score = 0, effective: total score 0–6, invalid: total score ≥ 6); overactive bladder symptom score (OABSS; if the urgent urination score > 2 and total score > 3, OAB will be diagnosed; mild: total score ≤ 5, moderate: total score 6–11, severe: total score ≥ 12). The CSESUSI will use a scoring method to record the changes of symptoms and signs before and after treatment, such as shivering, fever, dysuria, urinal pain, urinary urgency, urinary frequency, lower abdomen distending pain, lumbago, and percussion tenderness over kidney region. The SSST uses a scoring method to record the changes of symptoms, tongue, and pulse in TCM before and after treatment. The OABSS has been found to be reliable and valid and highly responsive to treatment-related fluctuations in overactive bladder symptoms. Repeating the test after an acceptable treatment interval is an effective way to assess the efficacy of a particular drug regimen on OAB symptoms [33, 34]. If the symptoms disappeared after seven days of treatment, it indicates that the patient is cured. If these symptoms partially disappeared after seven days of treatment, it indicates that the treatment is effective but not cured. If there was no obvious remission and the symptoms of infection persisted after seven days of treatment, it indicates that the treatment is invalid.

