#### Criteria of comprehensive efficacy

(i)Criteria of cure: the evaluation of clinical symptoms reached the level of cure after seven days of treatment; the value of urine leukocytes returned to the normal value; the original infected bacteria was cleared after seven days of treatment. All three criteria must be met.(ii)Criteria of effective treatment: the clinical symptoms were alleviated but did not reach the level of cure after seven days of treatment; the value of urine leukocytes was reduced but not returned to normal after seven days of treatment. Either of these criteria must be met.(iii)Criteria of invalid treatment: the clinical symptoms were not alleviated after seven days of treatment; the value of urine leukocytes was still higher than normal after seven days of treatment; the original infected bacteria were still cultured from the original infection position after seven days of treatment. All three criteria must be met.

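### Symptom response is labelled primary, but the trial is sized on an unspecified effective rate, and an unranked combined verdict classifies some of the same patients differently or not at all

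*Protocol article*

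**What the plan says.** Two places rank the endpoint. The abstract states: "The primary outcome measures of effective rate and recurrence rate are symptoms". In the body, the Primary outcome measure section under Effective rate judges symptoms at day 7: complete disappearance is cure, no obvious remission is invalid, and in between "If these symptoms partially disappeared after seven days of treatment, it indicates that the treatment is effective but not cured". Urine leukocytes and bacteriology come under Secondary outcome measure.

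Three other places do not carry that ranking through:

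- Sample size: "The effective rate will be taken as the main outcome measure of the clinical trial". No dimension is named. The one rate given, "it showed that the effective rate of SJT was 77.14% in the treatment of simple bacterial lower urinary tract infection", is not tied to a definition either.
- Effective rate: "The effective rate will be evaluated from three dimensions: symptoms; urine leukocytes; and bacteriological examination".
- Criteria of comprehensive efficacy, which follows the secondary outcomes, gives a combined cure, effective or invalid verdict and calls it neither primary nor secondary. Cure needs all three domains. Effective needs partial symptom relief or a partial leukocyte fall: "the value of urine leukocytes was reduced but not returned to normal after seven days of treatment. Either of these criteria must be met". Invalid needs failure everywhere: "the original infected bacteria were still cultured from the original infection position after seven days of treatment. All three criteria must be met".

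The two non-inferiority comparisons against control group 1 (Objective and design; Discussion) do not say which effective rate they test.

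**The concern.** Two complete sets of cure, effective and invalid criteria stand in the same part of the article, and either could be reported as the effective rate. They are not interchangeable. The combined rule lets a leukocyte fall alone make a patient effective, while the symptom rule calls that patient invalid. The aims are to show that Sanjin tablets can reduce or substitute antibiotics, so a rule that counts a patient with unrelieved symptoms as a success bears directly on the claim. An analyst applying the combined rule as printed would also meet patients with two classes and patients with none.

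**Working it through.** **1. The plan's own figure.** The Sample size section gives 77.14%, power 0.9, two-sided α = 0.01 and 76 per group. With no comparator rate or margin in the article, 76 cannot be derived, so it does not reveal which effective rate was meant. If both arms had 77.14%, the margin implied by 76 per group would be √[2 × 0.7714 × 0.2286 × (z₁₋α + z₀.₉)² / 76]: 26.3 points at one-sided 0.005, 22.1 points at one-sided 0.025. The point here does not rest on this.

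**2. Classification under both rules.** Cross symptoms (cured, partial relief, no relief) with leukocytes (normal, reduced but abnormal, not reduced) and culture (cleared, positive): 3 × 3 × 2 = 18 patterns. Success is taken as cure plus effective, which the article does not state. No obvious remission in the symptom rule is treated as the same as not alleviated in the combined rule.

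| Symptoms | Leukocytes | Culture | Patterns | Symptom rule | Combined rule as printed | Disagree on success |
|---|---|---|---|---|---|---|
| cured | normal | cleared | 1 | success | cure | no |
| cured | normal | positive | 1 | success | no class | **yes** |
| cured | reduced | either | 2 | success | effective | no |
| cured | not reduced | either | 2 | success | no class | **yes** |
| partial | any | either | 6 | success | effective | no |
| none | normal | either | 2 | failure | no class | no |
| none | reduced | cleared | 1 | failure | effective | **yes** |
| none | reduced | positive | 1 | failure | effective and invalid | **yes** |
| none | not reduced | cleared | 1 | failure | no class | no |
| none | not reduced | positive | 1 | failure | invalid | no |

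Disagreements: 1 + 2 + 1 + 1 = 5 of 18 (4 if the doubly classified pattern is settled as invalid). Patterns with no class: 1 + 2 + 2 + 1 = 6. These are counts of patterns, not of patients; the article gives no frequencies. The double classification arises because the leukocyte limb of invalid asks only for a value still above normal, which a reduced but abnormal value also meets.

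**3. Direction of the shift in the rate.** Assume 77.14% is a symptom success rate.

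- *Upward.* If no symptom-cured patient falls outside the classes and half of the symptom failures have a partial leukocyte fall: 0.7714 + 0.2286 × 0.5 = 88.6%.
- *Downward.* Assume independent domains; symptoms cured 50%, partial 27.14%, none 22.86%; leukocytes normal 50%, reduced 30%, not reduced 20%; culture cleared 80%. Success = 27.14 + 50 × (0.3 + 0.5 × 0.8) + 22.86 × 0.3 = 27.14 + 35.00 + 6.86 = 69.0%.

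**4. Effect on a comparison (all rates assumed).**

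- *Upward case, 76 per arm, symptom success 77.14% against 90%.* Difference −12.9 points; SE = √(0.7714 × 0.2286/76 + 0.90 × 0.10/76) = 0.0592; 95% lower limit −12.9 − 1.96 × 5.92 = −24.5. If 25%, 50% or 75% of symptom failures in both arms have a partial leukocyte fall, the combined difference is −9.6, −6.4 or −3.2 points, with lower limits −20.0, −15.1 or −9.5.
- *Downward case, control with 60% cured, 27.14% partial, 12.86% none (a 10-point symptom deficit).* With the same leukocyte and culture rates, control success = 27.14 + 60 × 0.7 + 12.86 × 0.3 = 73.0%, so the deficit is 4.0 points. With 95% clearance in control it is 27.14 + 60 × (0.3 + 0.5 × 0.95) + 12.86 × 0.3 = 77.5%, a deficit of 8.5 points.

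**The case against.** The strongest reply is that the article does rank the endpoint. The abstract and the subheadings place symptoms first and the laboratory domains second; the three dimensions can be read as introducing those ranked parts; and the combined verdict is never called primary, main or the effective rate. Nothing ties the non-inferiority tests to it. This stands. A reader might infer that the main outcome has two rival definitions and that the non-inferiority result therefore depends on the choice. The text supports only that it could.

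A reader might also infer that the either-or rule always lifts every arm toward 100% and hides a symptom deficit. The printed rule does not guarantee that. It counts leukocytes reduced but not normal, rather than any response, and it leaves some symptom-cured patients unclassified, so the combined rate can fall below the symptom rate.

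Third, the Exit criteria include patients whose symptoms are not alleviated or are aggravated, so some patients in the conflicting patterns may never reach a day-7 combined verdict. That could make those patterns rarer by an unknown amount. It does not remove the conflict, because the intention-to-treat set in Data analysis contains all randomized patients.

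Leaving the matter to an analysis plan or a fuller protocol is a weaker reply. The difficulty is not an omitted detail but two printed sets of criteria that disagree about the same patient.

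**Conclusion.** The point holds as a defect of specification and classification. Symptoms are labelled primary, but the sample size section and the three-dimension statement do not carry the label through, and the combined verdict has no rank. Read as printed, the two rules disagree on success in 5 of 18 patterns, one pattern is both effective and invalid, and six have no class. This needs no assumed rates, only the reading of success as cure plus effective.

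The effect on the non-inferiority conclusions is possible, not shown. The article states no margin, the definition behind 77.14% is not given, and the frequencies of the discordant patterns are unknown. In the assumed examples the lower limit moves from −24.5 points to between −20.0 and −9.5, and a 10-point deficit appears as 4.0 or 8.5. These figures show that the choice can matter; they do not estimate by how much. The change should be made before unblinding.

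**What to change.** 1. In Objective and design, Sample size and Effective rate, state that the main outcome for both non-inferiority comparisons is the symptom effective rate defined under Primary outcome measure, counted as cure plus effective.
2. Label Criteria of comprehensive efficacy as secondary.
3. Rewrite its three classes together so that they are mutually exclusive and exhaustive, and so that a leukocyte fall without symptom improvement is not effective. Changing "Either of these criteria must be met" alone is not enough: with invalid still requiring all three failures, a patient with no symptom relief, reduced leukocytes and a cleared culture would then have no class. One wording that works is: cure, all three criteria met; effective, symptoms improved or cured but not all cure criteria met; invalid, symptoms not alleviated. This puts the 18 patterns into 1, 11 and 6. The trial team must decide whether symptom-cured patients with a positive culture belong in effective.

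Cost: wording in the protocol and analysis plan before unblinding, with no new data. The combined classes change. The combined effective rate may be lower than under the printed rule, or higher if symptom-cured patients who now have no class are placed in effective. Under the example wording its success rate equals the symptom rate, so only its cure class would add information.
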